**Enrolment**						
Eligibility screening	X					
Informed consent	X					
Demographic data	X					
Case data	X					
Allocation		X				
**Treatment**						
**Assessments**						
PHQ-9						X
SF-36						X
Pain sensitivity specificity of acupoints			X		X	
Thermal specificity of acupoints			X		X	
Safety assessment						

PHQ-9, the Patient Health Questionaire-9 Items; SF-36, the MOS item short form health survey.

### Ethical approval

2.2.

The Ethics Committee of the Third Affiliated Hospital of Zhejiang Chinese Medical University granted consent (approval No: ZSLL-KY-2022-001-01-02). Each participant completed an informed consent form after receiving complete information about the experiment.

### Study participants

2.3.

To minimize the potential impact of gender and age on the biological characteristics of the 2 kinds of acupoint mentioned previously, this study will employ a gender- and age-matching strategy in the trial A, which involved the selection of HC participants and MDD patients.

### Inclusion and exclusion criteria

2.4.

The inclusion and exclusion criteria are summarized in details in Table 2.

**Table 2 tab2:** The inclusion criteria and exclusion criteria of participants of the study.

	Inclusion criteria	Exclusion criteria
HC group	(1) HC participants who could provide a recent depression screening report, and confirm they have not any cardiovascular, respiratory, digestive, urinary, hematological, endocrine, or neurological disease; (2) 18 ≤ age ≤ 60 years, male or female; (3) Participants have clear consciousness and could communicate with others normally; (4) Participants could understand the full study protocol and have high adherence. Written informed consent is signed by themselves.	(1) Participants with serious primary diseases of cardiovascular diseases, liver diseases, kidney diseases, urinary diseases, and hematological diseases; (2) Participants have a mental illness, alcohol dependence, or a history of drug abuse; (3) Pregnant or lactating participants; (4) Participants with intellectual disabilities who cannot cooperate with the questionnaire survey; (5) Participants with bleeding tendency, skin disease, allergic constitution, and allergic to adhesive tape; (6) The skin at the test site of participants has scars, hyperpigmentation, red and swollen; (7) Participants are participating in other trials.
MDD group	(1) Patients should meet the diagnostic criteria of the ICD-10 diagnostic criteria for MDD; (2) 18 ≤ age ≤ 60, male or female; (3) Participants have clear consciousness and could communicate with others normally; (4) Participants could understand the full study protocol and have high adherence. Written informed consent is signed by themselves.	(1) Participants with serious primary diseases of cardiovascular, respiratory, digestive, urinary, hematological, endocrine, neurological disease, and other serious primary diseases, and the disease cannot be effectively controlled clinically; (2) MDD caused by organic mental disorders, schizophrenia, bipolar disorder, psychoactive substances, and non-addictive substances; (3) Participants with suicidal tendencies; (4) Pregnant or lactating participants; (5) Participants with intellectual disabilities who cannot cooperate with the questionnaire survey; (6) Participants with bleeding tendency, skin disease, allergic constitution, and allergic to adhesive tape; (7) The skin at the test site of participants has scars, hyperpigmentation, red and swollen. IRT is not be performed on female subjects during their menstrual and ovulatory periods; (8) Participants are participating in other trials.

HC, Healthy control; MDD: Major depressive disorder; ICD-10, International Classification of Diseases 10th Edition.

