## Introduction

1.

Major depressive disorder (MDD) is a major public health problem and one of the primary causes of disease burden worldwide because of the high lifetime prevalence, high recurrence, and high disability rate (1–3). Due to the impact of COVID-19, there is a 27.6% increase in MDD patients worldwide in 2020, with female and young adults being the most affected (4). A previous study’s results suggest that people with chronic conditions are more likely to suffer from MDD (5), which causes more stress on the patient’s life.

The antidepressant medication is currently the most common method used to treat MDD. Although this therapy has achieved good clinical efficacy, it still has certain defects, such as delayed onset of action, long treatment period, high cost, and easy relapse when the medication is discontinued (6, 7). Those side effects may reduce adherence in MDD patients. Therefore, it is imperative to optimize the clinical treatment plan for MDD.

Acupuncture, as part of traditional Chinese medical (TCM), has been shown to have advantages for MDD (8, 9). Acupuncture has been recorded to treat emotional disorders since ancient times. Moreover, it was found that intradermal acupuncture (IA) improved the changes in vagal function, blood pressure, and Beck Depression Inventory scores in MDD patients (10). Our research team conducted data mining of clinical literature on acupuncture for MDD and found that the current acupoints for MDD treatment cover 14 meridian points and extraordinary acupoints, and the most commonly used points include GV20 (Baihui), LR3 (Taichong), PC6 (Neiguan), SP6 (Sanyinjiao), GV29 (Yintang), HT7 (Shenmen), ST36 (Zusanli), etc (11). Data mining results suggest that there were noticeable discrepancies in the selection of acupoints for MDD, and there is a lack of modern scientific evidence. Therefore, this study will select acupoints by objective detection of biological specificity of acupoints and evaluate the clinical efficacy of IA on MDD in a rigorous and standardized manner.

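### As written, Table 2 leaves the Trial A patient–control contrast open to confounding, because the comorbidity and cycle-timing rules differ between the two groups

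*Protocol article*

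**What the plan says.** Trial A compares 30 MDD patients with 30 healthy controls and is not randomized (protocol article, 2.5 and 2.9). Table 2 sets eligibility separately for each group.

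- **Comorbidity.** A control must "confirm they have not any cardiovascular, respiratory, digestive, urinary, hematological, endocrine, or neurological disease". For patients, exclusion (1) names the same seven organ systems but is limited to serious disease, ending "and other serious primary diseases, and the disease cannot be effectively controlled clinically".
- **Cycle timing.** MDD exclusion (7) adds a measurement rule to the skin criterion: "IRT is not be performed on female subjects during their menstrual and ovulatory periods". Control exclusion (6) has the same skin criterion and then passes straight to the next item: "The skin at the test site of participants has scars, hyperpigmentation, red and swollen; (7) Participants are participating in other trials".
- **Matching.** Section 2.3 says that "this study will employ a gender- and age-matching strategy in the trial A". It names no other factor.

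Sections 2.11.1 and 2.11.2 then take the four acupoints most associated with MDD on each test, by logistic regression, as PSA and TSA. These define two of the four Trial B arms.

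**The concern.** In an unrandomized comparison, a factor that the rules allow in one group and bar from the other can pass for an effect of diagnosis. Chronic disease and cycle phase are both plausible influences on the readings. The authors evidently regard cycle phase as relevant to skin temperature, since they wrote a rule about it. The Introduction also cites a study finding that "people with chronic conditions are more likely to suffer from MDD", so an imbalance in comorbidity is foreseeable.

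Two things depend on the contrast: which acupoints become PSA and TSA, and the stated aim of relating acupoint specificity to the diagnosis of MDD.

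**Working it through.** **1. Comorbidity rules compared.** Controls: no disease in seven organ systems, at any severity. Patients: excluded if the disease is serious and not effectively controlled. Even if every serious disease were excluded regardless of control, mild disease would still be admitted among patients and barred among controls.

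**2. Cycle rule compared.** It is present in the MDD row and absent from the parallel control criterion. The common test conditions in 2.11 cover room climate, rest, food, caffeine, alcohol, smoking and exercise, but not cycle phase. Read literally, a control woman may be imaged on a day when a patient may not. Only IRT, and hence TSA, is affected; pressure pain thresholds and PSA are not.

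**3. What could offset the difference.** There is no randomization. Matching on gender does not balance cycle phase, and matching on age and gender does not balance chronic disease. Section 2.16 names logistic regression for the screening and no covariate. A fuller analysis plan might add covariates, but ordinary adjustment would not help with a condition that controls cannot have by rule. With MDD status as the outcome, an indicator that is positive only in patients gives quasi-complete separation, and those patients stop informing the acupoint estimate. Restricting to comorbidity-free patients does the same openly. It would drop 0.2 × 30 = 6 to 0.3 × 30 = 9 patients at an assumed prevalence of 20–30%.

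**4. Scale.** The plan has no figure to reproduce, since 30 per group is given without an effect size, SD or power. As an illustration only, with prevalence and effect both assumed:

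- Shift = (prevalence in patients − 0 in controls) × effect in SD.
- 0.20 × 0.5 = 0.10 SD; 0.30 × 0.5 = 0.15 SD; 0.30 × 1.0 = 0.30 SD.
- Standard error of a difference with 30 per group = √(2/30) = 0.258 SD.
- Chance of p < 0.05 (two-sided, normal approximation) at a site with no MDD effect and shift b = 1 − Φ(1.96 − b/0.258) + Φ(−1.96 − b/0.258). This gives 5.0% at b = 0, 6.7% at 0.10, 8.9% at 0.15 and 21.3% at 0.30.
- For comparison, the difference detectable with 80% power is (1.960 + 0.842) × 0.258 = 0.72 SD.

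**5. From shift to selection.** Acupoints are taken by rank, not by significance. A shift of equal size at every site moves all the signed differences together and leaves their order unchanged. For the confounder to change which four are chosen, its effect must differ between sites. A common shift would still distort the apparent strength of association with MDD.

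**The case against.** Several counter-arguments have force.

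- **The cycle sentence may be a placement slip.** It speaks of female subjects, and 2.11 uses the word subjects for everyone tested. This stands as a caution: it may have been meant for all women. As printed it binds patients only, so its scope needs stating either way.
- **Strictly healthy controls against representative patients is a recognised design.** True, but the contrast then measures MDD together with its usual comorbidity, which is not how PSA and TSA are to be interpreted.
- **Controls' exclusion (1) also refers only to serious disease.** That does not help, because the stricter inclusion criterion must be met as well.
- **The analysis plan is not shown.** A reader might infer that no analysis can remove the imbalance. That goes too far: if comorbidity is recorded, ranking among comorbidity-free patients would address it.

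Other stronger readings are tempting but not supported.

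- A reader might add substance use, since controls are barred if "Participants have a mental illness, alcohol dependence, or a history of drug abuse". The patient row has a partial counterpart, excluding "MDD caused by organic mental disorders, schizophrenia, bipolar disorder, psychoactive substances, and non-addictive substances", and same-day alcohol and smoking are barred for everyone. What remains is too slight to carry weight. Barring mental illness in controls is inherent to the comparison.
- A reader might turn the length of the barred windows into a share of control women imaged inside them. The article gives no window length, and eligibility runs to age 60, so some women will be post-menopausal.
- A reader might think the cycle rule is missing from Trial B. Its participants are all MDD patients, already under the MDD row.

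**Conclusion.** The point holds as one of design exposure. Table 2 as written leaves the MDD-versus-control contrast open to confounding by comorbidity and, for IRT only, by cycle phase. Nothing else in the article closes that gap.

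A reader might infer that the contrast is confounded by a known amount, or that the wrong acupoints will be chosen. The article supports neither: it gives no prevalence of comorbidity and no effect of comorbidity or cycle phase on either measurement, so size and direction are unknown. The 0.10–0.30 SD range rests wholly on assumed inputs and would alter the ranking only through differences between sites. Nor is Trial B undermined as a randomized comparison; its arms remain validly compared whatever acupoints they contain. The loss is in how PSA and TSA are chosen and in reading them as specific to MDD.

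**What to change.** Make two changes before Trial A measurement starts, because the selected acupoints are then carried into Trial B.

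1. Move the cycle-timing sentence from the MDD row to 2.11, worded to cover every woman having IRT, controls included. Section 2.11 is headed as Trial A, so the wording should keep the Trial B patients covered, as they are now. Cost: some rescheduled control visits.
2. In Trial A, apply one common comorbidity rule to both groups. Alternatively, keep the present criteria, record comorbidity, and repeat the acupoint ranking among comorbidity-free patients. Cost: with a common strict rule, slightly slower recruitment of the 30 patients; with the restricted ranking, fewer patients in that analysis. Either way the acupoints are chosen, or checked, in a somewhat narrower group than Trial B enrols, and the report should say so.

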### Sample size estimation

2.5.

Since there are no relevant references for detecting the biological characteristics of MDD-related acupoints, we referred to the literature on acupoint detection (23, 27) and planned to recruit 30 MDD patients and 30 HC participants in trial A according to the principle of minimum sample size.

In Trial B, we did not estimate the sample size based on power calculations because there was no reference to indicate how effective the use of IA for MDD might be based on changes in the biological specificity of acupoints. To meet the need for minimum sample size, we instead recruited 120 participants.

### Recruitment

2.6.

Participants will be recruited from 3 hospitals, including the Third Affiliated Hospital of Zhejiang Chinese Medical University, the Affiliated Hangzhou First People’s Hospital, and Tongde Hospital of Zhejiang Province. Posters, local newspapers, and WeChat official account promotion will be the major means of recruiting strategies for participants. The PHQ-9 will be used as the initial screening tool to identify potential MDD patients. The final diagnosis of MDD will be made by a qualified psychiatry clinician based on a comprehensive evaluation of the patient’s medical history, symptoms, and other factors that may affect their eligibility. Eligible participants will be informed about the study’s specific requirements. After signing the informed consent form, participants are invited to join the study.

### Termination criteria and management

2.7.

Subjects with one of the following conditions will be terminated: (1) serious adverse reactions that make continued participation in the trial inadvisable; (2) serious complications or deterioration conditions during the study require urgent emergency measures; (3) requesting to withdraw from the trial midway; (4) pregnancy; and (5) poor compliance and inability to follow the study protocol. When a subject has terminated, the investigator should contact the subject as soon as feasible by door-to-door, telephone appointment, or letter whenever possible. The investigator should record in detail the reason and time of termination from the study, complete the assessment items that can be completed, and those who have exceeded 1/2 course of treatment should be entered into the efficacy statistics.

### Elimination criteria

2.8.

Subjects with any of the following conditions will be eliminated: (1) not meeting the inclusion criteria but being mistakenly enrolled in the trial; (2) not following the treatment of the study protocol or having incomplete data, which affects the assessment of efficacy and safety; (3) poor compliance and withdrawing from the study on their own; (4) receiving other treatment than the intervention of this trial.

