### Statistical Analysis

2.16.

Statistical analyses will be performed by a third-party statistician not involved in the pre-test using the statistical software SPSS 25.0 (SPSS Inc., Chicago, IL, United States). It will be expressed as counts and percentages for categorical variables. Continuous variables in normal distribution will be expressed as mean ± standard deviation, while skewed data will be expressed as median and interquartile range. The chi-Squared test will be used to compare group differences in dichotomous variables with baseline characteristics such as gender and age. Logistics regression analysis will be used to screen potentially superior acupoints. To analyze changes in continuous variables at multiple time intervals before and after the intervention, normally distributed data will be compared within and between groups using repeated measures analysis of variance (ANOVA). For within- or between-group comparisons, non-parametric test will be utilized for skewed distribution data. Statistical significance is defined as a *p* value <0.05.

The intention-to-treat approach will be adopted. Missing data (imputation of missing cases by regression and imputation from the last observation) and non-compliance will be subjected to sensitivity studies (analysis by protocol).

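### The elimination rule (2.8) and half-course rule (2.7) are not confined to a per-protocol set and so conflict with the intention-to-treat analysis declared in 2.16

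*Protocol article*

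**What the plan says.** Three sections of the protocol article bear on who is analysed in Trial B.

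- **2.16, Statistical Analysis.** "The intention-to-treat approach will be adopted". Missing data are to be imputed by regression and from the last observation, and "non-compliance will be subjected to sensitivity studies (analysis by protocol").
- **2.8, Elimination criteria.** Besides subjects enrolled by mistake (criterion 1), subjects are to be eliminated for "not following the treatment of the study protocol or having incomplete data, which affects the assessment of efficacy and safety" (criterion 2), "poor compliance and withdrawing from the study on their own" (criterion 3), or "receiving other treatment than the intervention of this trial" (criterion 4).
- **2.7, Termination criteria and management.** Subjects are terminated for serious adverse reactions, deterioration needing emergency measures, withdrawal, pregnancy, or "poor compliance and inability to follow the study protocol". The investigator is to complete whatever assessments can be completed, and "those who have exceeded 1/2 course of treatment should be entered into the efficacy statistics".

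Section 2.16 does not mention 2.7 or 2.8 and does not define a modified intention-to-treat set. Sections 2.7 and 2.8 do not mention a per-protocol set.

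**The concern.** Criteria 2 to 4 of 2.8, and every termination reason in 2.7, arise after allocation. Some can depend on outcome: a patient who deteriorates or has a serious adverse reaction before mid-course is, by implication of 2.7, left out of the efficacy statistics. Some can depend on arm: non-compliance with needling cannot arise in the waiting-list group, which has none during the study.

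Two analysts following this text could therefore build different primary data sets, one of all randomised patients and one of those who survived 2.7 and 2.8. Only the first keeps the comparison that randomisation protects. If the choice is left open, it may be made once the data are visible.

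**Working it through.** **1. The sections side by side.** The plan gives no figure to reproduce, so the check begins with the text.

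| Randomised patient | 2.16 (ITT) | 2.7 | 2.8 |
|---|---|---|---|
| Terminated for deterioration before half the course | analysed | by implication not in the efficacy statistics | no criterion on deterioration itself |
| Poorly compliant, withdraws after half the course | analysed | entered | eliminated (criterion 3) |
| Receives other treatment | analysed | not addressed | eliminated (criterion 4) |
| Incomplete data that affect assessment | analysed, imputed | not addressed | eliminated (criterion 2) |

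In every row 2.16 disagrees with at least one of the other two sections. In the second row 2.7 and 2.8 also disagree with each other.

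**2. Inputs for an illustration of size.**
- From the document: 120 patients allocated 1:1:1:1, so 120 / 4 = 30 per arm; significance at p < 0.05. The 120 has no power calculation behind it: "To meet the need for minimum sample size, we instead recruited 120 participants". No dropout allowance is stated.
- Assumed: two-sided test, SD of PHQ-9 change 5 points, no true effect, excluded shares pA and pB, and a gap D by which excluded patients' change is worse than that of retained patients, equal in both arms. A plain two-arm comparison of mean change stands in for the planned repeated-measures ANOVA.

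**3. Formulas.** If the full-arm mean improvement is m, then p × (excluded mean) + (1 − p) × (retained mean) = m. With retained minus excluded equal to D, the retained mean is m + pD. The spurious difference between arms is therefore

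b = D × (pB − pA),

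in favour of the arm that loses more patients. With nA and nB retained, SE = 5 × √(1/nA + 1/nB), and the rejection rate under no effect is Φ(−1.96 + b/SE) + Φ(−1.96 − b/SE).

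**4. Results.**

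10% against 30% excluded: 27 and 21 retained, SE = 5 × √(1/27 + 1/21) = 1.455.
- D = 2: b = 2 × 0.20 = 0.4; b/SE = 0.275; type I error 5.9%.
- D = 4: b = 0.8; b/SE = 0.550; type I error 8.5%.
- D = 6: b = 1.2; b/SE = 0.825; type I error 13.1%.

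10% against 20% excluded, D = 4: 27 and 24 retained, SE = 1.403; b = 0.4; b/SE = 0.285; type I error 5.9%.

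A simulation of 6,000 runs under the same assumptions gave 9.1% (10% v 30%, D = 4), 12.5% (10% v 30%, D = 6) and 5.3% (10% v 20%, D = 4), in line with the formula.

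**5. Precision.** If both compared arms lose 20%, 24 of 30 remain in each. Power for an assumed 0.8 SD difference then falls from 87% to 79%, and for 0.5 SD from 49% to 41%.

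**The case against.** The best defence is that the sections can be reconciled. Section 2.16 sends non-compliance to a per-protocol sensitivity analysis, which makes sense only if non-compliers are in the main set. Section 2.8 never says what subjects are eliminated from, so it could be the definition of the per-protocol set. In 2.7, that patients short of half the course stay out is implied, not stated. Detailed analysis sets are also often left to a statistical analysis plan, which is not at hand.

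Part of this stands: the conflict disappears if 2.7 and 2.8 are confined to the per-protocol set. But the document does not confine them. Section 2.7 already covers stopping participation and speaks of efficacy statistics without qualification, and criterion 2 of 2.8 is tied to assessing efficacy and safety. Removal from the analysis is the natural reading. These are rules the protocol states, not details it leaves out.

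A reader might infer more than the text supports:

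- *That intention-to-treat cannot be carried out.* It can, once the rules are confined as above.
- *That nothing is left to impute.* Criterion 2 covers only incomplete data that affect assessment, criterion 3 requires poor compliance together with withdrawal, and terminated patients past half the course are expressly kept. Some patients with missing visits would remain.
- *That half a course has no meaning on the waiting list.* Section 2.12 gives every group a course of up to 6 weeks, so half can be read as 3 weeks in all arms.
- *That waiting-list patients are the likeliest to be lost.* Nothing in the document says so. They receive antidepressant treatment and are offered needling afterwards.

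**Conclusion.** The conflict is real and concerns who enters the primary PHQ-9 comparison. As written, 2.7 and 2.8 can remove randomised patients for post-allocation reasons, they contradict 2.16, and they contradict each other in at least one case.

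Neither the size nor the direction of any bias can be derived from the document, which gives no SD, dropout rate or outcome gap. If poor-outcome patients were removed mainly from a needle arm, its effect would look larger; if mainly from the waiting list, smaller. The figures of 0.4 to 1.2 points and about 6 to 13% type I error need a threefold imbalance in exclusions. A milder imbalance with a 4-point gap leaves the error close to nominal. They show that the effect need not be trivial with 30 per arm, and should not be read as a forecast. The case for changing the text rests on the contradiction itself.

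**What to change.** 1. In 2.16, state that the primary analysis set is all 120 randomised patients in the arm assigned, regardless of compliance, sessions received, other treatment or missing visits.
2. In 2.7 and 2.8, state that the elimination criteria and the half-course rule serve only to define the per-protocol sensitivity set. Say which of the two governs a poorly compliant subject who withdraws after half the course. Criterion 1 should be judged only on data available before randomisation, by someone masked to arm.
3. Extend the existing instruction in 2.7 to complete available assessments, so that PHQ-9 and SF-36 are collected at the scheduled weeks 3, 6 and 10 after intradermal acupuncture stops, unless consent is withdrawn. Outcomes not collected then cannot be recovered.

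This concerns only who is analysed and followed up; it leaves the reasons for stopping treatment as they are. The cost is a few sentences in three sections and a small number of additional questionnaires.
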